**Aim #1:**

Detection of mutations in untreated subjects over time

**Figure 5:** Baseline HIV-1 drug resistance testing will be performed using OLA and consensus sequencing on the first available specimens from subjects with acute and very early HIV-1 infection who enroll in the PIC cohort and from subjects previously enrolled in the cohort who meet eligibility criteria for study. ARV-naïve subjects with mutations detected at baseline will provide specimens to determine the detection of mutations over time (**Aim #1**). Subjects both with and without HIV-1 drug resistance at baseline who initiate ARV therapy during follow-up will provide specimens to determine whether increased levels of HIV-1 drug resistance mutations are detected in PBMCs during ARV therapy and whether low-frequency mutations impact the response to ARV therapy (**Aim #2**). Subjects enrolled in the PIC Cohort study will refer potential source partners to the PIC Partners study. Partners will be asked to provide blood and genital specimens in order to compare patterns of HIV-1 drug resistance within transmission pairs (**Aim #3**).

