**Aim #2: Quantify the increase in detection of low-frequency mutations in PBMCs during ARV therapy.**

Primary objectives:

1) Compare the proportion of subjects with transmitted HIV-1 drug resistance that have new HIV-1 drug resistance mutations detected in PBMCs 6 and 12 months after the start of ARV therapy compared to subjects without transmitted HIV-1 drug resistance at baseline.

2) Evaluate time to virologic suppression in subjects with transmitted HIV-1 drug resistance compared to subjects without transmitted HIV-1 drug resistance.

Secondary objectives:

1) Explore whether the timing of ARV therapy impacts the increased detection of low-frequency mutations, time to virologic suppression, or time to virologic failure.

2) Explore whether specific mutations (e.g. M184V) are selected for by ARV therapy and are found at a greater level over time within treated subjects with and without HIV-1 drug resistance at baseline.

3) Explore whether specific HIV-1 drug resistance mutations are associated with significant differences in time to virologic suppression and time to virologic failure compared to subjects without transmitted HIV-1 drug resistance.

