**5.c.2 Aim #2: Quantify the increase in detection of low-frequency mutations in PBMCs during ARV therapy.**

The primary objectives of the study described in this aim will evaluate changes in the detection of low-frequency mutations in PBMCs over time during ARV therapy and the virologic consequences of ARV therapy in the setting of transmitted low-frequency HIV-1 drug resistance. We hypothesize that, over time, additional mutations will be detected in a greater proportion of treated subjects with transmitted drug resistance compared to treated subjects without HIV-1 drug resistance detected at baseline, because the relative level to which viral replication is suppressed will be diminished in the former group. Secondary analyses will explore associations between specific HIV-1 drug resistance mutations, the interval between HIV-1 acquisition and the start of ARV therapy, the increased detection of HIV-1 drug resistance mutations, and treatment outcomes including time to virologic suppression and time to virologic failure.

This longitudinal study will evaluate subjects enrolled in the PIC cohort within 30 days of the estimated date of HIV-1 infection, who initiate ARV therapy at any point following the baseline evaluation, and who achieve undetectable HIV-1 RNA levels (less than 50 copies/mL) within six months after the start of ARV therapy. OLA will be performed using PBMCs collected at the visit immediately prior to the start of ARV therapy (unless this visit is within 4 weeks from the baseline specimen) and in specimens obtained 6 and 12 months following the start of treatment. The detection of a new mutation will be defined as any mutation detected during follow-up that was never previously detected. Additional analyses will use the semi-quantitative nature of OLA to evaluate the changes in levels of mutations during ARV treatment (i.e. <5%, 5-10%, 10-30%, 30-50% >50% of the viral quasi-species) and the reappearance of mutations that had been detected at baseline but were lost to detection prior to the start of ARV therapy in the absence of ARV selection pressures.

**Table 9: Sample size needed in each arm to detect a difference in proportion of subjects with new low-frequency mutations**

|  | | Percent of subjects with low-frequency mutations at baseline who have new mutations detected after start of ARVs | | | |
| --- | --- | --- | --- | --- | --- |
| 20% | 30% | 40% | 50% |

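### Aim 2: the 4-week waiver gives early ARV starters one fewer pre-treatment PBMC test, which inflates their count of 'new' mutations and biases the exploratory timing analysis

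*Protocol*

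**What the plan says.** All of this is in the protocol.

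- **Who enters Aim 2.** Section 5.c.2 admits subjects "who initiate ARV therapy at any point following the baseline evaluation", so early and late starters are pooled.
- **Tests before ARVs.** Every subject has a baseline test. A PBMC test at the last pre-ARV visit is added, "unless this visit is within 4 weeks from the baseline specimen".
- **Tests on ARVs.** PBMCs are tested "in specimens obtained 6 and 12 months following the start of treatment", the same for all.
- **Endpoint.** A new mutation is "any mutation detected during follow-up that was never previously detected". The definition does not fix which earlier tests, or how many, count.
- **Use of timing.** Secondary objective 1 of Aim 2 (section 5.b) is to "Explore whether the timing of ARV therapy impacts the increased detection of low-frequency mutations". Section 5.c.2 lists ARV timing among the factors in an exploratory logistic regression of new mutations, to be run if enough subjects have them.
- **Overlap with Aim 1.** The Figure 5 legend says that ARV-naïve "subjects with mutations detected at baseline will provide specimens to determine the detection of mutations over time". Those tests are at 6 and 12 months after infection. Subjects without baseline mutations do not get them.

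**The concern.** Whether a mutation counts as new depends on how many chances there were to find it before ARVs. The waiver ties that number to the time of ARV start, and time of ARV start is then examined as a predictor of new mutations. Adjustment could hardly separate the two, because the number of tests is almost a function of timing. The protocol neither equalises the tests nor allows for the difference.

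The likely direction is towards more new mutations with early treatment. Section 3.d already raises the worry that treatment in acute infection may select for or generate resistance mutations. An artefact of test counts would look like support for it.

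The Aim 1 tests add a second asymmetry. A late starter with baseline resistance may have been tested again at 6 or 12 months. A late starter without baseline resistance has not. The extra tests can only remove new mutations from the resistant group, which works against the hypothesis of primary objective 1.

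**Working it through.** **1. The plan's own figure.** Table 9 gives 35 without and 18 with baseline resistance for 10% versus 50%, at alpha 0.05 (taken as two-sided) and 80% power. With allocation r = 0.5, the pooled proportion is (0.10 + 0.5 × 0.50)/1.5 = 0.233. The uncorrected size is [1.96 × √(3 × 0.233 × 0.767) + 0.842 × √(0.09 + 0.25/0.5)]² / 0.40² = 27.1, so 28. With the continuity correction it is (27.1/4) × [1 + √(1 + 3/(27.1 × 0.5 × 0.40))]² = 34.2, so 35, and 18 in the smaller group. The figure reproduces. The issue here is the endpoint definition, not the sample size.

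**2. Model with no ARV effect.** Assume a mutation persists at a constant level and each test finds it independently with probability d. With k pre-ARV tests and two on-ARV tests:

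P(called new) = (1-d)^k × [1 - (1-d)²]

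| d (assumed) | k = 1 | k = 2 | ratio 1/(1-d) |
|---|---|---|---|
| 0.25 | 0.75 × 0.4375 = 33% | 25% | 1.33 |
| 0.50 | 0.50 × 0.75 = 38% | 19% | 2 |
| 0.75 | 0.25 × 0.9375 = 23% | 6% | 4 |

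These are chances per persisting mutation, not per subject. Counting baseline plasma as a further test for everyone lowers both columns and leaves the ratio unchanged.

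**3. Subject-level size from Table 4d.** OLA was positive in PBMCs only in 8 subjects, in plasma only in 14 and in both in 12. A two-sample capture-recapture estimate gives 20 × 26/12 = 43.3 carriers per 100, of whom 43.3 - 34 = 9.3 were missed in both compartments. PBMC detection is d = 12/26 = 0.46.

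- Early: 0.0933 × [1 - 0.538²] = 6.6%.
- Late: 6.6% × 0.538 = 3.6%.

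**4. Mutation-level size from Table 5.** The rows sum to 25 in PBMCs only, 24 in plasma only and 8 in both. The estimated total is 33 × 32/8 = 132, so 132 - 57 = 75 were missed per 100 subjects, with d = 8/32 = 0.25.

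- Early: 0.75 × 0.4375 = 0.328 new mutations per subject. With a Poisson count, 1 - e^(-0.328) = 28% of subjects have at least one.
- Late: 0.328 × 0.75 = 0.246 per subject, or 22% of subjects.

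**5. When the direction would reverse.** Let L be the mutations missed at baseline and A those that arise between baseline and the pre-ARV visit. Late starters show more only if (1-d)(L + A) > L, that is A > L × d/(1-d). This is 0.33 L at d = 0.25 and 0.86 L at d = 12/26.

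**6. How often the waiver applies.** In the pilot (section 4.g) baseline specimens were taken at a median of 29 to 30 days after infection, and ARVs started at a median of 45 days (IQR 24-107). Table 11 has visits at Weeks 4 and 8 and none between, so a subject who starts before Week 8 usually has a last scheduled visit inside the waiver. It would apply often, but the exact share cannot be derived from these medians.

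**The case against.** The strongest points on the other side are these.

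- **The timing analysis is exploratory and weak.** True. With 53 subjects split 27 and 26, power for differences of the size in steps 3 and 4 is about 7 to 8%. The harm is a biased estimate more than a false significant result.
- **The tests may not be independent.** A variant lying stably under the 5% cutoff is missed every time, and the second test then adds little. Plasma/PBMC discordance is also partly biological, so d from Tables 4d and 5 may understate repeat detection in PBMCs. These points change the size. The ratio stays above 1 unless the second test never finds what the first missed, or nothing is ever missed.
- **The limitation is disclosed.** Section 5.f.1 concedes that OLA cannot tell pre-existing low-level mutations from newly developed ones. It does not say that this misclassification differs by ARV timing.
- **The pilot may not represent the new subjects.** It favoured ARV starters and was not restricted to enrolment within 30 days. This stands, and limits what can be said about the frequency of the waiver.

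A reader might infer that the artefact feeds directly into the protocol's argument for deferring ARVs. The text does not support that. The Aim #2 implications in section 2 and the end of section 3.d rest deferral on mutations that decay before ARVs and do not reappear, which is a separate analysis. The caution in section 3.d about selecting or developing mutations during acute treatment is the closer link.

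A reader might also infer that primary objective 1 is broadly compromised. It is touched only where a late starter with baseline resistance also had Aim 1 tests. Section 5.c.2 projects its new treated subjects from those starting in the first year, so this is a limited part of the 18.

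**Conclusion.** The concern holds in limited form. The waiver and the open-ended definition together give early starters one fewer pre-ARV PBMC test. With imperfect detection and no ARV effect this inflates their new mutations by 1/(1-d) per persisting mutation. At subject level the pilot-based gap is about 3 points (6.6% versus 3.6%) or 6 points (28% versus 22%). It would be wrong to read the per-mutation ratios of 1.3 to 4 as ratios of affected subjects, or as what would be seen if ARVs truly select mutations, since real selection dilutes them.

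The estimates assume constant mutation levels, independent tests, and plasma/PBMC discordance as a proxy for missed detection. Decay before a late start would change the size. The main damage is to the exploratory timing analysis. The effect on primary objective 1 is smaller, confined to some late starters, and against the study's hypothesis.

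**What to change.** 1. Delete the 4-week waiver. Give every treated subject the same pre-ARV reference set: baseline plasma and PBMC OLA, plus one further pre-ARV PBMC OLA on the last pre-ARV specimen, or on a second baseline aliquot if there is only one visit.
2. In the main analysis, define a new mutation as one found on ARVs and not detected in that common set.
3. Keep baseline plasma in the set. In the pilot, 14 of the 34 OLA-positive subjects were positive in plasma only. Under a PBMC-only reference their known mutation could later be called new. That could happen only in the baseline-resistant group, and would tilt primary objective 1 towards its hypothesis.
4. Report two sensitivity analyses: (a) the current definition, which also counts the extra Aim 1 specimens, and (b) the last pre-ARV PBMC specimen alone as the reference. Because of item 3, (b) is informative for timing more than for primary objective 1.

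With equal tests the early-to-late ratio under the model is 1 for any d. Equal counts do not equalise the interval between tests, so decay or new mutations before a late start remain a matter of interpretation. The cost is one OLA on a stored specimen per early starter and a revised definition. There are no new visits or patients, and the planned 53 treated subjects stand.

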**4.b University of Washington Primary Infection Clinic (PIC)**

Since 1992, *319* subjects with HIV-1 infection have been enrolled and followed for a median of *42 (range 0-184)* months in an observational cohort at the PIC. **Table 2** shows the demographic characteristics of subjects with primary HIV-1 infection enrolled in the PIC cohort compared to persons with predominantly established HIV-1 infection reported to Public Health - Seattle & King County [181]**.** *Seventy-eight subjects* were enrolled within 30 days of their estimated dates of HIV-1 infection. *Women and African/African-American subjects are under-represented relative to the number of individuals diagnosed with HIV-1 infection in King County because the majority of individuals comprising these categories are African immigrants who did not acquire their infection locally. Additional details regarding the inclusion of women and minorities are provided in* ***8. Protection of Human Subjects.***

ARV treatment was started in some subjects through non-randomized research protocols or through primary care providers. Despite the existence of national guidelines that have recommended the consideration of therapy during acute HIV-1 infection, the proportion of PIC subjects starting therapy immediately following HIV-1 acquisition has decreased over time, likely due to an increasing number of studies that have found no direct evidence of sustained clinical benefits in subjects treated during primary HIV-1 infection*. Forty-eight (67%) of 72 subjects enrolled in 1999-2001, 40 (68%) of 59 subjects enrolled in 2002-2004, and only 22 (39%) of 57 subjects enrolled in 2005-mid 2008 chose to receive ARV therapy in the first year after HIV-1 acquisition.* Plasma and PBMCs are stored and available for each of these subjects throughout study follow-up, and records of CD4+ T-cell counts, HIV-1 RNA levels, and clinical endpoints are available at regular intervals.

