| Percent of subjects with no mutations at baseline who have new mutations detected after start of ARVs | 10% | *316/158* | *102/51* | *54/27* | *35/18* |
| 20% | *-* | *461/231* | *133/67* | *66/33* |
| 30% | *-* | *-* | *559/280* | *153/77* |
| 40% | *-* | *-* | *-* | *609/305* |

alpha = 0.05, power = 80%

The sample size for this aim will be motivated by a two-sample test of proportions that will compare the percentages of subjects with low-frequency mutations at baseline who have new mutations detected during ARV therapy compared to the percentage in subjects who had no mutations detected at baseline (**Table 9**). Estimates for the sample size calculations were informed by two small studies that identified increased numbers of HIV-1 drug resistance mutations in two (22%) of nine [32] and six (40%) of 15 [33] ARV-naïve subjects during ARV therapy. Based on these calculations and assuming that one-third of subjects will have transmitted drug resistance, a sample size of *53* treated subjects (*18 subjects with and 35 without drug resistance detected at baseline*) will have 80% power to detect a significant difference in the two groups if 50% of the subjects with baseline mutations and 10% of the subjects without baseline mutations have additional HIV-1 drug resistance mutations detected in PBMCs after the start of ARV therapy. There were 20 subjects who were studied as part of the pilot project who enrolled in the PIC Cohort study within 30 days of HIV infection, received ARV therapy for at least six months, and achieved virologic suppression. Another *twenty* subjects have enrolled in the PIC Cohort since the pilot study began and have received treatment *for at least six months*. If we estimate that *33*% of newly-enrolled subjects will initiate ARV therapy *in the first year of* follow-up *and assume a 10% loss-to-follow-up rate in the first year*, we would need to enroll *42* subjects in addition to these *40* subjects in order to achieve the desired sample size of *53* treated subjects (***Figure 5***)*.*

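### Aim 2's stated need for 42 new enrollees is too low: it omits the aim's own suppression criterion and does not show that the 20 post-pilot subjects qualify

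*Protocol*

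**What the plan says.** Protocol section 5.c.2 defines the Aim 2 population by entry to the cohort within 30 days of the estimated infection date, ARV start at any time after baseline, and virologic response: subjects "who achieve undetectable HIV-1 RNA levels (less than 50 copies/mL) within six months after the start of ARV therapy". OLA on PBMCs follows "in specimens obtained 6 and 12 months following the start of treatment".

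The sample size rests on Table 9 ("alpha = 0.05, power = 80"%). "assuming that one-third of subjects will have transmitted drug resistance", the section asks for 53 treated subjects, 18 with and 35 without baseline resistance, to detect 50% versus 10% with new mutations.

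The supply of those 53 has three parts:

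- **Pilot, 20 subjects.** Entry within 30 days, at least six months of ARVs and virologic suppression are all stated, though no six-month limit is put on the suppression.
- **Post-pilot, 20 subjects.** These "subjects have enrolled in the PIC Cohort since the pilot study began and have received treatment" for at least six months. Nothing is said about 30-day entry or suppression.
- **New enrollees, 42.** The yield uses 33% starting ARVs in the first year and 10% loss to follow-up.

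Elsewhere, section 5.a plans 80 prospective enrollees for Aims 1 and 2 together, and section 5.c.1 asks for 72 for Aim 1.

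**The concern.** The criteria and the count of subjects stand in the same section but do not match. Suppression by six months defines who may enter the analysis, yet it is stated for only one of the three sources, and there without the time limit. The sentence on the pilot subjects names both 30-day entry and suppression; the next sentence, on the post-pilot subjects, names neither. The new-enrollee yield has no term for suppression.

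The three parts add up to almost exactly 53, so there is no margin. Any subject who fails a criterion takes the eligible number further below the target for the first primary objective of Aim 2. Someone monitoring recruitment against the 42 would stop counting too early.

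**Working it through.** **1. The target of 53.** Inputs from section 5.c.2: p1 = 0.10, p2 = 0.50, alpha 0.05, power 80%, ratio k = 0.5 (one with baseline resistance to two without). Sidedness is not stated for Aim 2; two-sided is assumed because it reproduces the table.

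- Pooled proportion: (0.10 + 0.5 x 0.50)/1.5 = 0.233.
- Uncorrected n without resistance: [1.960 x sqrt(3 x 0.233 x 0.767) + 0.842 x sqrt(0.09 + 0.25/0.5)]^2 / 0.40^2 = 27.1, that is 28 and 14.
- With the continuity correction: (27.1/4) x [1 + sqrt(1 + 2 x 1.5/(27.1 x 0.5 x 0.40))]^2 = 34.2, that is 35 and 18.

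This is the plan's 35/18, total 53. The other cells of Table 9 also reproduce with the continuity correction. The target and its 80% power are right.

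**2. The stated supply.** 42 x 0.33 x 0.90 = 12.5, and 40 + 12.5 = 52.5. The 42 therefore contains two factors only. Solved for the 13 subjects needed, 13/(0.33 x 0.90) = 43.8, so 44. The gap from 42 to 44 is close to rounding; the missing suppression factor matters more.

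**3. Supply under the plan's criteria.** Let s be the proportion suppressed by six months and f the share of the 20 post-pilot subjects who entered within 30 days. The protocol gives neither, so both are assumptions. The 20 pilot subjects are taken as fully eligible.

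- Eligible number with m new enrollees = 20 + 20sf + 0.297ms
- Enrollees needed for 53 = (33 - 20sf)/(0.297s)

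For f = 1 and m = 42, at one-third resistant and 50% versus 10%:

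| s | Eligible | Groups (without/with) | Power, continuity-corrected | Power, Fisher exact | New enrollees needed for 53 |
|---|---|---|---|---|---|
| 1.00 | 52.5 | 35/17 | 80% | 87% | 44 |
| 0.95 | 50.9 | 34/17 | 80% | 86% | 50 |
| 0.90 | 49.2 | 33/16 | 77% | 84% | 57 |
| 0.80 | 46.0 | 31/15 | 74% | 82% | 72 |

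The corrected power is the normal probability of (d - c - 1.96 x SE0)/SE1, with d = 0.40 and c = 0.5 x (1/n1 + 1/n2). At 31/15, SE0 = 0.132, SE1 = 0.140 and c = 0.049, giving 0.65 and a power of 74%. At the full 35/18 the same formula gives 82%, and Fisher's exact test 88%.

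**4. Against the planned enrollment.** With f = 1, 53 is reached when s is at least 33/(20 + 0.297m): 0.80 for m = 72 and 0.75 for m = 80. With 80 enrollees, the eligible number is 61.6, 59.4 or 55.0 at s = 0.95, 0.90 or 0.80.

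If f is below 1 the cover is thinner. With 80 enrollees, 53 requires f of at least (33/s - 23.76)/20: 0.46 at s = 1, 0.65 at s = 0.90 and 0.87 at s = 0.80.

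**The case against.** The best defence is that 42 is only Aim 2's minimum and the project plans more. That stands: at 72 to 80 enrollees the gap closes if s is about 0.75 to 0.80 or more and all post-pilot subjects are 30-day entrants. It does not make 42 correct, because section 5.c.2 states it as the number needed.

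On 30-day entry, section 5.c.1 describes 54 post-pilot enrollees and 15 expected ones. Its wording that all entered within 30 days could cover only the 15, but its arithmetic covers all 69: 69 x 0.34 x 0.66 = 15.5, against the stated 15. Section 5.d.1 also requires screening within 30 days for ongoing enrollment. This supports f = 1 as the plan's working assumption, but section 5.c.2 does not state it for the 20 it counts.

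On suppression, 83 pilot subjects started ARVs (section 4.g) and four had virologic failure (section 5.c.2). If the four are among the 83, 79/83 = 95% did not fail. This is an imperfect proxy, since the 24-week failure threshold is 400 copies/mL rather than 50. Section 3.d says only that suppression usually succeeds.

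Two further points stand. ARV starts after the first year are eligible, while the 33% covers first-year starters only, so supply is somewhat understated. And the plan names only a two-sample test of proportions: with f = 1 and 42 enrollees, Fisher's exact test keeps at least 80% power down to s of about 0.75.

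A reader might also infer from section 4.b, where "only 22 (39%) of 57 subjects enrolled in 2005-mid 2008 chose to receive ARV therapy in the first year after HIV-1 acquisition", that the 20 post-pilot subjects are nearly every treated enrollee of that period and so cannot all be early entrants. The documents do not support this: the two counts use different enrollment windows and treatment definitions, and section 4.b gives no infection stage for those 57.

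**Conclusion.** The statement that 42 new enrollees plus 40 in hand give 53 Aim 2 subjects is wrong under the plan's own criteria. It falls just short with complete suppression (44 needed) and further short at any lower rate: about 50, 57 or 72 enrollees at assumed suppression of 0.95, 0.90 or 0.80, with all post-pilot subjects taken as 30-day entrants.

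A reader might go on to infer that Aim 2 loses its 80% power, or that the 53 itself is wrong. Neither follows. The 53, the 18/35 split and the 80% reproduce. The post-pilot 20 may all qualify. Whether power drops below 80% depends on two proportions the protocol does not give, on the test used and on whether 42 or 80 are enrolled. Loss of power is possible, not shown. What remains is a misstated enrollment requirement for a primary objective.

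**What to change.** Check the 40 subjects in hand against both criteria in section 5.c.2 (entry within 30 days; below 50 copies/mL within six months of ARV start) and report how many pass. Add the suppression proportion seen in the pilot to the new-enrollee yield. Replace the 42 with the resulting requirement, and state the eligible number and power expected from the 80 enrollees planned in section 5.a. Keep the 53, the 18/35 and the 80% as the target.

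The cost is a database check and restated text, with no added procedures. Correcting the figure does not itself require anyone extra to be enrolled. The downside is that the stated requirement, and perhaps the expected power, may look less favourable.
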